## Methods

### Study design

Surgical treatment for antiplatelet intracerebral hemorrhage (SAP-ICH) is an ongoing and multicenter study; the flow chart of which is shown in Fig. 1. Beginning in September 2019, this trial is scheduled to be completed by December 2022. Due to unknown and hugely potential intracranial hemorrhage complications after neurosurgery, ethical issues need to be taken into account; therefore, the randomized controlled trial was not suitable currently. The purpose of this study is to evaluate the effect and safety of emergency surgery for SSICH patients on LOAPT, with the focus placed on four aspects: (1) the outcome of operated SSICH patients on LOAPT; (2) the risk of intraoperative and postoperative hemorrhagic complications; (3) the risk of developing postoperative ischemic diseases for SSICH patients on LOAPT; (4) the methods to assess the coagulation state of operated SSICH patients on LOAPT.

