### Outcomes and study endpoints

All patients will be closely monitored until death or 6 months after the occurrence primary hemorrhage. In this study, the following outcomes will be taken into consideration (Table 3). The primary outcome is the total mortality, including in-hospital and out-of-hospital mortality. The second outcome is the postoperative hemorrhagic complication, and the PIB is our main focus. The functional outcome of patients is another outcome interesting us and will be assessed using modified Rankin scale (mRS). The postoperative adverse cardiovascular/cerebral events (ACCE) include the region of original stroke enlarging, new ischemic stroke occurring outside the operative region, myocardial infarction, repeated revascularization, and deep venous thrombus. The screening, evaluation, and follow-up schedules are detailed in Table 4.

**Table 3 Tab3:** Outcomes to be taken in consideration

(1) Total mortality; (2) postoperative hemorrhagic complication; (3) patients’ functional outcome; (4) postoperative adverse cardiovascular/cerebral events (ACCE).

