### Study definition

After admission, all of the patients would receive standardized care according to the guidelines. Severe spontaneous intracerebral hemorrhage (SSICH) is confirmed by both severe intracerebral hemorrhage radiologically and clinical coma (GCS < 13).

In definition, “on long-term oral antiplatelet therapy (on LOAPT)” refers to patients that received oral antiplatelet treatment on a continued basis for more than 7 days and discontinued antiplatelet medication no more than 7 days after the occurrence of hemorrhage. Antiplatelet therapy involved aspirin, clopidogrel, and dual antiplatelet treatment. Postoperative intracerebral bleeding (PIB) was defined as rehemorrhage within the operative region or new intracerebral hemorrhage associated with the operation on radiological examination.

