### Data collection

In case the patients meet our criteria, all information, including the demography, clinical information, preoperative radiological data, intraoperative findings, and laboratory and TEG data, will be recorded on the case report form (CRF). After being discharged, all the patients were followed up on a regular basis by outpatient visit and on telephone 3 months and 6 months after primary hemorrhage, respectively. During each follow-up visit, the survival condition, mRS, ACCE, and medication will be recorded. If the patients feel unable to undergo radiological examination in the participating center, a follow-up cranial image will be required. Once radiological examination is completed, the patients’ imaging data will be transmitted to the Tiantan hospital (this center will work as an imaging interpretation center) to reconfirm several events, including SSICH, PIB, and postoperative ischemic disease. During the study, the researchers are required to protect privacy for the patients and ensure the confidentiality of their medical information. The information collection schedule is presented in Table 4.

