All statistical analyses were conducted with the assistance of SPSS (Version 22.0, IBM, American). The data was indicated as mean (x) ± standard deviation (SD) for normally distributed data, median, and interquartile range (IQR) for skewed distributed data or number (*n*) and percentage (%). In this study, two main comparative groups and an observational cohort will be established, as shown in Fig. 1. Firstly, in order to investigate the effect of emergency neurosurgery, a comparison will be performed between SSICH patients on LOAPT receiving conservative treatment and those receiving emergency neurosurgery. Secondly, in order to investigate the safety of emergency neurosurgery, a comparison will be performed between operated SSICH patients on LOAPT and those not on LOAPT. Thirdly, in order to investigate the intra/postoperative complications and the risk of ischemic disease after discontinuing antiplatelet treatment, the characteristics of SSICH patients on LOAPT will be analyzed; moreover, because the history of previous neural ischemic events or cardiac events could affect the risk of postoperative ischemic events, we would perform the subgroup analysis depending on this history to further investigate the effect of discontinuing antiplatelet treatment on the risk of ischemic disease. The difference will be compared by conducting χ^2^ test, Mann-Whitney *U* tests, or Student’s *t* tests. The independent risk factors were analyzed by logistic regression, while the factors with *p* < 0.10 in univariate analysis were entered into a multivariate logistic regression model. The result was indicated as odd ratio (OR) and 95% confident interval (CI). The receiver operating characteristic (ROC) curve analysis was performed to test the prediction value of different parameters and different methods. An area under the curve (AUC) in a ROC analysis of ≥ 0.7 is considered as a clinical utility, while *p* value of < 0.05 was treated as statistically significant.

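### The univariate p < 0.10 screen, the only covariate rule for the only adjusted analysis, does not keep out variables that arise after treatment

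*Protocol article*

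**What the plan says.** The relevant text of the protocol article is short.

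- **Group comparisons (Results).** "The difference will be compared by conducting" a chi-square, Mann-Whitney or t test. These are unadjusted.
- **Regression (Results).** The regression is presented as a search for independent risk factors. The entry threshold is a p value below 0.10, and the factors that meet it "in univariate analysis were entered into a multivariate logistic regression model". Results are to be given as ORs with 95% confidence intervals. The modelled outcome, the candidate variables and the place of the exposure in the model are not stated.
- **Recorded data (Data collection).** Baseline and later items share one form: "preoperative radiological data, intraoperative findings, and laboratory and TEG data, will be recorded". Adverse cardiovascular/cerebral events (ACCE) and medication are added at the follow-up visits.
- **PIB (Study definition; Outcomes and study endpoints).** PIB is "rehemorrhage within the operative region or new intracerebral hemorrhage associated with the operation on radiological examination", so by definition it needs an operation. It is the main focus of the second outcome. The Background says that intraoperative and postoperative bleeding can be fatal.
- **Design (Study design).** Patients are not randomised, because "the randomized controlled trial was not suitable currently".

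**The concern.** Without randomisation, a crude comparison of operated and conservatively treated patients is open to confounding by indication. Readers will therefore look to whatever adjusted estimate is published, and this regression is the only adjusted analysis named. A significance screen picks strong predictors of the outcome, whether they precede treatment or result from it.

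PIB, intraoperative findings, ACCE and later medication all arise after the treatment decision. If surgery can kill through PIB, a mortality model that contains PIB no longer estimates the whole effect of surgery. Its surgery coefficient sets operated patients who did not bleed against all conservative patients. In the safety comparison, intraoperative bleeding may lie on the path from LOAPT to PIB, so adjusting for it could remove part of the contrast under study.

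This differs from omitting confounders. Forcing in a list of baseline variables does not help if the screen is kept alongside it and can still add post-treatment factors.

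**Working it through.** The protocol prints no OR or adjusted estimate, so there is no figure of that kind to reproduce. The crude OR below follows from its planning rates.

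**Inputs from the protocol (Results)**
- Mortality on LOAPT: 30% operated, 45% conservative.
- PIB in operated patients on LOAPT: 23%.
- Planned groups: 100 operated and 120 conservative patients on LOAPT.

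**Assumptions**
- Mortality among PIB patients, *m*, is not given. It is varied below.
- PIB is coded as absent in every conservative patient. The protocol does not say so.
- Baseline confounding is left out, to isolate the effect of entering PIB.

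**Crude OR**

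(0.30/0.70) / (0.45/0.55) = 0.4286 / 0.8182 = 0.52.

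**OR with PIB in the model**

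No conservative patient has PIB, so the PIB term absorbs the operated patients who bled. The surgery OR becomes the odds of death in operated patients without PIB divided by the odds in conservative patients. Mortality in operated patients without PIB is *q* = (0.30 − 0.23*m*) / 0.77, and the OR is [*q*/(1 − *q*)] / 0.8182.

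| *m* (assumed) | *q* | OR for surgery |
|---|---|---|
| 30% | 0.300 | 0.52 (no shift) |
| 50% | 0.240 | 0.39 |
| 60% | 0.210 | 0.33 |
| 70% | 0.181 | 0.27 |

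**No true effect of surgery (45% mortality in both groups)**

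Here *q* = (0.45 − 0.23*m*) / 0.77, and the true OR is 1.

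| *m* (assumed) | *q* | OR for surgery |
|---|---|---|
| 45% | 0.450 | 1.00 (no shift) |
| 60% | 0.405 | 0.83 |
| 70% | 0.375 | 0.73 |
| 80% | 0.345 | 0.65 |

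**Would PIB pass the screen?**

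This was simulated at 100 against 120 patients, with at least 3,000 studies per scenario and an uncorrected chi-square test of PIB against death.

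- At the plan's mortality rates, PIB passes p < 0.10 in about 34, 73 and 96% of studies for *m* = 50, 60 and 70%.
- With no true effect, it passes in about 45, 83 and 98% for *m* = 60, 70 and 80%. A significant false benefit of surgery then appears in about 6, 16 and 30% of studies, against a nominal 2.5% in that direction.

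**Safety comparison**

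The plan's PIB rates of 23% and 10% give a crude OR for LOAPT of (0.23/0.77) / (0.10/0.90) = 2.69. How far this would fall with intraoperative bleeding in the model depends on how much of the LOAPT effect runs through that bleeding. The protocol gives nothing on this. If the whole effect is assumed to run through it, the adjusted OR is 1.0 by construction, so that figure is no estimate of size.

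**The case against.** The strongest reply is that the protocol does not describe the model that would do this damage. The regression is worded as a search for independent risk factors. No candidates, outcome or treatment term are named, and the tests named for the group comparisons are unadjusted. A reader might infer that the model does contain PIB and so adjusts surgical harm away, or that this regression supplies the study's two main answers. The documents support neither inference: recording an item on the form does not make it a candidate in every model.

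Three further points carry weight.

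- PIB and intraoperative findings have no natural value in conservative patients. If left blank, those patients drop out of a complete-case fit and there is no surgery coefficient to distort.
- Within operated patients, intraoperative factors can be reasonable candidates in a prognostic model of PIB, which may be all that is meant.
- The size rests on a mortality after PIB that the protocol never gives. At 30% there is no shift at the plan's own rates.

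It can also be said that a candidate list belongs in the analysis plan, which is not shown. That answers a complaint about a missing list. It does not answer this point, because the article states the entry rule itself, and that rule is unsuitable for any model from which an effect is to be read.

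**Conclusion.** The point holds in conditional form. The single stated covariate rule permits adjustment for consequences of treatment, and nothing in the article prevents it. The direction of the resulting bias in a mortality model is clear if three conditions are met: PIB is coded as absent in conservative patients, it passes the screen, and PIB patients die more often than other operated patients. The surgery OR then moves towards benefit. Over assumed PIB mortalities of 50 to 70% the shift is from 0.52 to between 0.39 and 0.27. With no true effect, assumed mortalities of 60 to 80% give 0.83 to 0.65. For LOAPT and PIB, entering intraoperative bleeding could weaken the contrast, by an amount that cannot be sized from the documents. It is not established that the planned analysis will do either. The rule should still be corrected, because the study is non-randomised and no other adjusted analysis is named.

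**What to change.** In the statistical part of Results, state that any model used to estimate the effect of surgery on death, or of LOAPT on PIB:

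- always includes the exposure;
- uses prespecified covariates known before the treatment decision (mortality model) or before incision (PIB model);
- uses these in place of the p < 0.10 screen, not in addition to it.

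State also that PIB, ACCE, intraoperative findings and later medication are not adjusted for in the mortality model, and that ACCE, intraoperative findings and later medication are not adjusted for in the PIB model. These factors can be examined in a separate, descriptive risk-factor model from which no surgery or LOAPT effect is claimed.

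The cost is one or two sentences, with no new data or patients. The effect model may explain somewhat less variance.

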**Results:**

In this study, two comparative cohorts and an observational cohort will be set up. The primary outcome is the effect of emergency surgery, which is subject to assessment using the total mortality and comparison in the survival rate of SSICH patients on LOAPT between surgical treatment and conservative treatment. The second outcome is the safety of surgery, with the postoperative hemorrhagic complication which is compared between the operated SSICH patients on and not on LOAPT. Based on the observation of the characteristics and outcome of SSICH patients on LOAPT, the ischemic events after discontinuing LOAPT will be further addressed, and the coagulation function assessment system for operated SSICH patients on LOAPT will be established.

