## Results

China National Clinical Research Center for Neurological Diseases will be responsible for data analysis. Sample size was calculated by using PASS (Version 15, NCSS corporation, American). All sample size calculations were performed by conducting two-sided test, *α* = 0.05 and *β* = 80% (the degree of control = 80%). In this study, two comparison groups will be established, with the primary and secondary outcomes as the focus in this study. According to our unpublished data collected from 7 participating centers in 2019, for SSICH patients on LOAPT, the total mortality was about 30% for operated patients and 45% for the patients receiving conservative treatment, with the ratio of two groups reaching about 1:1.5. Moreover, for operated SSICH patients, the incidence of PIB was about 23% for patients on LOAPT and 10% for patient not on LOAPT, with the ratio of two groups reaching about 1:2.5. With regard to the primary outcome, our sample size was calculated as 196 (196 SSICH patients on LOAPT, operation group: *n* = 78; conservation group: *n* = 118). As for the secondary outcome, the sample size was 247 (247 operated SSICH patients, LOAPT group: *n* = 70; non-LOAPT group: *n* = 177). Moreover, in order to establish the coagulation function assessment system, the area under curve was expected to be 0.7, and the sample size was set to 92 (92 operated SSICH patients on LOAPT, PIB group: *n* = 23; non-PIB group: *n* = 69). In this case, a minimum of 387 SSICH patients (includes 118 patients on LOAPT receiving conservative treatment, 92 patients on LOAPT receiving emergency surgery, and 177 patients not on LOAPT receiving emergency surgery) may be required in this study to reach our research objective. Thus, to ensure final statistics, a total of 400 patients (patients on LOAPT receiving conservative treatment, *n* = 120; patients on LOAPT receiving emergency surgery, *n* = 100; patients not on LOAPT receiving emergency surgery, *n* = 180; Fig. 1) will be recruited. In this study, 10% of patients would be lost during follow-up. Finally, we decided to recruit 450 appropriate patients.

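### The only adjusted effect measure named is an odds ratio, while the primary question is about mortality rates and 30–45% of patients are expected to die; an adjusted risk difference and risk ratio should be added.

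*Protocol article*

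**What the plan says.** - **Question.** The abstract (Results) describes the primary outcome as total mortality and a "comparison in the survival rate of SSICH patients on LOAPT between surgical treatment and conservative treatment". The section Outcomes and study endpoints also makes total mortality the primary outcome and follows patients to death or 6 months. The Study design section explains that randomisation was judged unsuitable.
- **Expected risks.** The sample-size paragraph under Results states, for patients on LOAPT, that "the total mortality was about 30% for operated patients and 45% for the patients receiving conservative treatment".
- **Analysis.** The statistical paragraph under Results first sets out the group comparisons. Categorical data are shown as number and percentage, and differences are tested by chi-square, Mann-Whitney or t test. Logistic regression follows, described as an analysis of independent risk factors, with covariates entered at univariate p < 0.10. The sentence on the effect measure comes directly after: "The result was indicated as odd ratio (OR) and 95% confident interval (CI").
- **Not named.** No adjusted risk, risk difference or risk ratio appears.

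**The concern.** Treatment is chosen by clinicians and families, so the crude comparison of mortality is open to confounding and the adjusted estimate will carry the weight. Under the stated plan the figures on the risk scale are unadjusted, and the adjusted figure is on the odds scale.

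Two properties of the odds ratio matter here. First, death is common, so the odds ratio does not approximate the risk ratio and lies further from 1. Secondly, it is noncollapsible: conditioning on prognostic factors moves it away from 1 even when those factors are unrelated to treatment. Univariate and multivariable results will both exist under this plan. Anyone who sets them side by side on the odds-ratio scale sees a change that mixes confounding with noncollapsibility.

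The Discussion says the study is meant to help surgeons decide whether to operate. That decision turns on absolute mortality, and the plan names no adjusted estimate of it.

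**Working it through.** **Inputs from the article (Results, sample-size paragraph).** Mortality 30% operated and 45% conservative; planned recruitment of 100 operated and 120 conservative LOAPT patients before the allowance for loss to follow-up.

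**The plan's own figure.** The article states no expected odds ratio, risk ratio or risk difference. The figure it builds on these risks is the primary sample size ("196 SSICH patients on LOAPT, operation group: *n* = 78; conservation group: *n* = 118"), from a two-sided 5% test with 80% power and "with the ratio of two groups reaching about 1:1.5". With k = 1.5 and a pooled risk of (0.30 + 1.5 × 0.45)/2.5 = 0.39:

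n(operated) = [1.96 √(0.39 × 0.61 × (1 + 1/1.5)) + 0.842 √(0.30 × 0.70 + 0.45 × 0.55/1.5)]² / 0.15² = (1.234 + 0.515)²/0.0225 ≈ 136, or 137 after rounding up.

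With 206 conservative patients the total is 343, so 196 is not reproduced. At 78 and 118 the power is about 56%. The stated group sizes fit 30% versus 50% (78 + 117). This is a separate matter, but it prompts the sensitivity check in step 1.

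**Step 1: the three measures at the stated risks.**
- Risk difference = 0.30 − 0.45 = −0.15.
- Risk ratio = 0.30/0.45 = 0.667, a 33% lower risk.
- Odds ratio = (0.30/0.70)/(0.45/0.55) = 0.4286/0.8182 = 0.524, 48% lower odds.

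If conservative mortality were 50%, the risk ratio would be 0.60 and the odds ratio 0.4286/1 = 0.43. The gap does not depend on which rate is right.

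**Step 2: what a report would show with 30/100 and 54/120 deaths.**
- Odds ratio: SE(log) = √(1/30 + 1/70 + 1/54 + 1/66) = 0.285; 95% CI 0.30 to 0.92.
- Risk ratio: SE(log) = √(1/30 − 1/100 + 1/54 − 1/120) = 0.183; 95% CI 0.47 to 0.95.
- Risk difference: SE = √(0.21/100 + 0.2475/120) = 0.0645; 95% CI −27.6 to −2.4 points.

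**Step 3: noncollapsibility without confounding.** Assume a normal prognostic score with SD s on the log-odds scale, independent of treatment. For each group, solve for the intercept a such that the average of 1/(1 + exp(−(a + s·x))) over standard normal x equals 0.45 (conservative) or 0.30 (operated). The conditional odds ratio is exp(a_operated − a_conservative). The article gives no value for s; the range is assumed.

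| Assumed s | Approx. c-statistic of the score | Adjusted OR | Standardised RR | Standardised RD |
|---|---|---|---|---|
| 0 (crude) | – | 0.524 | 0.667 | −15 points |
| 0.5 | 0.63 | 0.505 | 0.667 | −15 points |
| 1 | 0.74 | 0.460 | 0.667 | −15 points |
| 1.5 | 0.81 | 0.405 | 0.667 | −15 points |
| 2 | 0.86 | 0.349 | 0.667 | −15 points |

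The standardised measures stay put because the marginal risks are unchanged. The odds ratio moves although there is nothing to correct.

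**The case against.** The strongest reply is that nothing here is an error. An odds ratio with a 95% interval from logistic regression is a conventional and valid measure for a binary outcome. Three stronger readings are tempting, and the article supports none of them.

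- *That the primary answer overstates the mortality reduction.* The article ties the odds ratio to the risk-factor model and does not call it the primary estimate. Group mortality will be reported as percentages, from which the crude risk difference and risk ratio follow. An odds ratio overstates only if it is read as a risk ratio, and the article does not read it so.
- *That a crude-to-adjusted shift says nothing about confounding.* A shift may well contain confounding; it cannot be attributed to confounding alone. Nor does the article plan to judge confounding this way.
- *That other adjusted measures are excluded.* The article names none, but it does not rule them out, and a fuller plan may contain them.

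It is also fair that the size in step 3 rests on assumed values; at s = 0.5 the shift from 0.524 to 0.505 is negligible.

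What remains is that the article does state its choice of effect measure, so the point concerns a stated choice and not only silence. If the logistic model is not meant for the treatment comparison, then no adjusted treatment estimate is named at all, and the same addition is needed.

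**Conclusion.** The point holds as a minor one. For a mortality question in a non-randomised comparison, the only adjusted measure named is not on the scale of the question. On the article's own risks the distance is firm: odds ratio 0.52 against risk ratio 0.67, with a risk difference of −15 points. The direction of the noncollapsibility effect is also firm. Its size is not: about 0.51 to 0.35 for the adjusted odds ratio, resting on an assumed log-odds SD of 0.5 to 2 and a score unrelated to treatment. The planned odds ratio does not have to be withdrawn or demoted, and no rule for judging confounding is needed.

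**What to change.** Keep the logistic model and the odds ratio. For surgery versus conservative treatment, add one sentence to the analysis text: from the fitted model with treatment included, predict 6-month mortality for all LOAPT patients, once as operated and once as conservatively treated; average each set; and report the two standardised risks, the adjusted risk difference and the adjusted risk ratio, with 95% confidence intervals by bootstrap or delta method.

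The cost is a little more programming, possibly outside SPSS 22, and a relative figure that looks less striking than the odds ratio. No new data or patients are needed. The change does not remove residual confounding: standardised results are only as good as the covariates in the model, and selecting these by univariate p < 0.10 remains a limitation.

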### Thrombelastography (TEG) test and coagulation function assessment system

TEG is performed to monitor the function of platelet with the assistance of Thrombelastograph Coagulation Analyzer (TEG model 5000, Haemoscope Corporation, Niles IL, American). All parameters, including maximum amplitude (MA, mm), citric acid kaolin tracing (CK), reptilase tracing (A), aspirin tracing (AA), and clopidogrel tracing (ADP), are recorded through standard tracing. Based on MA, the rate of platelet inhibition was calculated using the formula as shown below:
$$ AA/ ADP\%=\frac{\mathrm{MA}\left(\mathrm{CK}\right)-\mathrm{MA}\left(\mathrm{A}\mathrm{A}/\mathrm{ADP}\right)}{\Big(\mathrm{MA}\left(\mathrm{CK}\right)-\mathrm{MA}\left(\mathrm{A}\right)} $$

where AA% represents the inhibition to platelet caused by aspirin, and ADP% indicates the inhibition to platelet caused by clopidogrel. Further with traditional coagulation test including bleeding time, prothrombin time, activated partial thromboplastin time, and fibrinogen as well as TEG, we plan to establish a combined coagulation function assessment system in order to assess the surgical risk facing SSICH patients on LOAPT, with the focus placed on PIB. Moreover, for the patients not on LOAPT, it is considered that these patients have normal platelet function and do not need to undergo further relative test.

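### Clinical utility is declared from a bare AUC point estimate of 0.7, the value the study itself expects: about a coin toss for one real marker, and too lenient for a combined system fitted and judged on the same patients

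*Protocol article*

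**What the plan says.** All of this is in the Protocol article.

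- **Aim** (section on the TEG test and coagulation function assessment system): "we plan to establish a combined coagulation function assessment system in order to assess the surgical risk". The ingredients are bleeding time, prothrombin time, activated partial thromboplastin time, fibrinogen and TEG; the outcome of interest is PIB.
- **Size** (Results, sample-size paragraph): "the area under curve was expected to be 0.7, and the sample size was set to 92", split as "PIB group: *n* = 23; non-PIB group: *n* = 69". The general settings are "All sample size calculations were performed by conducting two-sided test", alpha 0.05 and "the degree of control = 80"%. The article labels the last figure beta; I read it as 80% power.
- **Selection** (Results, statistical paragraph): factors with p below 0.10 in univariate analysis go into a multivariable logistic model.
- **Evaluation** (same paragraph): "The receiver operating characteristic (ROC) curve analysis was performed to test the prediction value of different parameters and different methods". An AUC of 0.7 or more "is considered as a clinical utility", and p below 0.05 is significant.

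The article attaches no confidence limit to the 0.7 rule and sets aside no validation patients.

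**The concern.** The pass mark equals the AUC assumed to be true, and it is compared with a point estimate. A sample that can show that a marker beats chance is not a sample that can show that it reaches 0.7. The rule also makes no distinction between a single laboratory value and a model whose variables and weights are chosen from the same few bleeds; the AUC of such a model is biased upwards when measured on the patients used to build it.

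The system is meant to assess surgical risk in emergency patients on antiplatelet drugs. A combination that predicts poorly in new patients could be published as clinically useful, and a single marker that truly performs as planned could be dismissed.

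**Working it through.** **Inputs.** From the article: 23 PIB and 69 non-PIB, expected AUC 0.7, two-sided 0.05, power 80%, "the incidence of PIB was about 23% for patients on LOAPT", univariate screen at p < 0.10. Assumed: null AUC 0.5; 6 to 10 candidate predictors (four conventional tests plus several TEG values; the article fixes no number); independent normal predictors; the combined system is the screened logistic model, this being the only selection rule stated.

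**1. Reproducing the 92.** Hanley-McNeil variance with m events and n non-events:

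Var(A) = [A(1−A) + (m−1)(Q1−A²) + (n−1)(Q2−A²)]/(mn), where Q1 = A/(2−A) and Q2 = 2A²/(1+A).

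For m = 23, n = 69 (mn = 1587):
- A = 0.7: Q1 = 0.5385, Q2 = 0.5765; (0.21 + 22×0.0485 + 68×0.0865)/1587 = 0.00451; SE = 0.067.
- A = 0.5: Q1 = Q2 = 1/3; (0.25 + 22/12 + 68/12)/1587 = 0.00488; SE = 0.070.
- Power against 0.5: Φ[(0.2 − 1.96×0.0699)/0.0672] = Φ(0.94) = 82.6%.

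At the stated 23% incidence, 0.23×92 = 21.2, so 21 and 71. The SEs are then 0.0696 and 0.0721, and power is Φ[(0.2 − 1.96×0.0721)/0.0696] = Φ(0.84) = 80.0%. At that incidence 92 is the smallest total that reaches 80%. The figure is thus reproduced, as a test against 0.5.

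**2. One prespecified marker, no fitting (23/69).**
- True AUC 0.70: 95% limits 0.70 ± 1.96×0.067 = 0.57 to 0.83. P(estimate ≥ 0.7) = 50%; 51% in 20,000 simulated data sets.
- True AUC 0.65: 24%. True AUC 0.60: 8%.
- Useless marker: z = 0.2/0.0699 = 2.86, so it passes about 0.2% of the time (0.4% in simulation).
- Significance at 0.05 needs only 0.5 + 1.96×0.0699 = 0.637. Any estimate of 0.7 is already significant, so the p-value condition adds no protection.

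**3. Combined model of pure noise, built and judged on the same 92** (3,000 data sets per row; Monte Carlo SE at most √(0.25/3000) = 0.9 points):

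| Candidates | AUC ≥ 0.7 after p < 0.10 screen | AUC ≥ 0.7, all entered |
|---|---|---|
| 4 | 4% | 8% |
| 6 | 7% | 21% |
| 8 | 10% | 41% |
| 10 | 16% | 58% |
| 15 | 30% | 91% |

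**4. Combined model with real signal, all candidates entered.** When the best achievable AUC is 0.7, spread over 4, 8 or 12 predictors, the AUC on the building data passes in 72%, 91% and 97% of data sets. The fitted models' mean AUC in new patients is 0.67, 0.65 and 0.63.

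**5. Effect of optimism correction** (full models with 6, 8 or 11 candidates, 250 data sets each). Noise passes fall from 21%, 38% and 68% to 1.2%, 0.8% and 2.8%. With a best achievable AUC of 0.7, passes fall from 79%, 87% and 95% to about 36 to 37%. I did not simulate the correction with the screen repeated inside each resample.

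**The case against.** **Validation may be planned elsewhere.** This is a condensed article. It neither calls the AUC uncorrected nor rules out internal validation, and bootstrap detail often sits in a fuller plan. This stands: the leniency fault is conditional on the analysis being as the article describes it. The threshold fault is not, because the published rule itself sets a point estimate against the planning value.

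**The large noise figures describe models that the article does not specify.** This also stands. The only stated selection step is the p < 0.10 screen, so 7 to 16% is the relevant range. The 21 to 58% applies only if every candidate is entered, and both ranges move with a predictor count that the article leaves open.

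**The consequence is limited.** This is the fourth of four aims in Study design, care is not altered by the study (Ethics and public involvement), and the Discussion leaves the indications for surgery and the choice of platelet-function tool unresolved. This is fair as to weight. But the Discussion also calls the assessment system a crucial aim, and the utility label will be read outside the study.

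**Stronger readings to avoid.** A reader might infer that one and the same AUC both passes on noise and fails half the time when the assumption is true. It does not: the coin toss belongs to an unfitted single marker, which passes on noise less than 0.5% of the time, while a fitted combination passes too often. A reader might also infer that the lower confidence limit must reach 0.7. At 23/69 that needs an observed AUC of about 0.81, and at a true AUC of 0.70 no sample size gives adequate power, so it is an option and not a necessary correction.

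**Conclusion.** The point holds as two separate faults of one rule. For a single prespecified marker that truly has the planned AUC of 0.70, the rule is met about 50% of the time, although the sample has about 80 to 83% power against an assumed null of 0.5. For a combined system selected, fitted and judged on the same patients, the rule is too lenient: about 7 to 16% of screened pure-noise models with 6 to 10 candidates earn the utility label, and 21 to 58% without screening.

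The first result rests on the Hanley-McNeil variance and the 23/69 split. The second rests on an assumed number of independent normal candidates and on no validation beyond what the article describes. The 23 bleeds are a planning figure: 23% of 92 is about 21, and 23% of the 100 operated patients on antiplatelet treatment to be recruited is 23. The primary mortality comparison and the PIB comparison are not affected. The point should be put right before the coagulation system is analysed.

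**What to change.** 1. Judge the combined system on the bootstrap optimism-corrected AUC, repeating variable selection and fitting in every resample, and report its 95% CI.
2. State that 92 patients are sized to support AUC above 0.5 and do not establish AUC of 0.7 or more; name the null used in the calculation.
3. Replace the bare point-estimate rule: describe a system or marker whose 95% CI includes values below 0.7 as exploratory pending external validation.
4. Report single prespecified markers separately from fitted combinations.

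Penalised regression and a formal lower-limit pass mark at 0.7 are optional.

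Cost: analysis-plan wording and a bootstrap run on data already being collected, with no extra patients. The reported AUC will be lower and a utility claim less likely. With an achievable AUC of 0.7, the corrected estimate reached 0.7 in only about 36 to 37% of simulated full-model data sets, so an exploratory label is the likely outcome if the planning assumption is right.
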